#### Objective assessment of self-weighing/adherence (intervention group)

As an objective measure of compliance, the intervention group will be given weighing scales (BodyTrace, USA) that objectively record weight every time participants weigh themselves and then this information is remotely transmitted back to the research team at the University of Birmingham. These scales are only included as an objective process measure of adherence to self-weighing and we will not provide any feedback to participants, nor will we monitor changes in weight during the trial follow-up period.

#### Weight record cards (intervention group)

The intervention group will complete weight record cards and we will collect these from participants as a measure of intervention implementation at the follow-up visit. The record cards will also tell us how much of the intervention was delivered by practice nurses per protocol.

#### Perceptions of regular self-weighing (intervention group)

In the intervention group, we will use five items from Steinberg’s Daily Self-Weighing Perceptions Questionnaire^46^ to measure perceptions of regular monitoring of weight at follow-up.

#### Use of the POWeR online programme (intervention group)

Using participants’ unique usernames POWeR automatically records participants’ usage of the website (eg, pages visited, when/for how long, goals and weights entered and dates).

#### Attendance at immunisation appointments (both groups)

To ensure the intervention does not have an adverse impact on women attending the immunisation appointments all practices will be asked to provide data on all immunisation appointments attended by both groups. Any missed appointments will be investigated and a reason allocated by the GP surgery. We will also collect patient reported attendance at the immunisation appointments at the follow-up visit.

### Assessment of harms

We will not be collecting adverse events for this trial. Serious adverse events (SAEs) which are attributable to the trial intervention will be documented and reported from the date of consent into the PIMMS-WL study until 30 days after the 3-month follow-up visit. SAEs or deaths related to pre-existing medical conditions are not considered related to the trial intervention and are therefore excluded from notification as SAEs.

### Withdrawal

Participants will be aware that they can freely withdraw from the trial (or part of) at any time. Details of withdrawal will be clearly documented. Different types of withdrawal are defined as:

The participant would like to withdraw from trial treatment but is willing to be followed up in accordance with the schedule of assessments.The participant would like to withdraw from trial treatment and is not willing to be followed up or for any further data to be collected.The participant wishes to withdraw completely and is not willing to have any of their data, including that already collected, to be used in any future trial analysis.

The details of withdrawal (date, reason and type of withdrawal) should be clearly documented in the source data.

If a recruited GP practice withdraws from participation in the trial prior to randomisation, they may be replaced by another practice. If a practice withdraws after randomisation, consideration will be given to replacing with another practice.

### Statistical analysis

A separate statistical analysis plan will provide a more comprehensive description of the planned analyses. A brief outline of the planned analyses in relation to the stop-go criteria is provided below. The data analysis for this feasibility trial will be descriptive and mainly focus on CI estimation, with no hypothesis testing performed.

The recruitment rate will be presented as a percentage based on the number of participants who took part in the trial divided by the target recruitment (n=80). BWCH will also provide data on the number of invitation letters sent, along with data on the age and ethnicity (in summary format) of the women who were sent an invitation letter.

The quantitative assessment of whether the intervention is acceptable will be based on the adherence of women to weekly self-weighing and use of the online POWeR programme. In the first instance, the objective recording of weight on the scales will be used to assess the frequency of self-weighing/adherence.

In addition, to check that the intervention has no adverse impact on infant immunisation rates, the proportion of babies who attended all three immunisation appointments will be reported for each practice (both groups) and the rate compared with the normal immunisation rate for the practice. Reasons for missed appointments will be summarised descriptively. Recruitment, adherence and immunisation rates will be summarised as proportions with 95% CIs.

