### Sample size and recruitment

This is a feasibility trial therefore a formal sample size calculation has not been conducted. The trial is not designed or powered to detect a statistically significant difference in effectiveness between the two treatment groups.

We will recruit 10 to 12 GP practices (clusters) across Birmingham, UK, and the list of participating practices will be held by Birmingham Clinical Trials Unit (BCTU). We will then aim to recruit 80 participants from these GP practices over 8 months. Potentially eligible participants will be identified initially from medical records at Birmingham Women’s and Children’s NHS Foundation Trust (BWCH). Initial screening of medical records by BWCH will confirm the women is aged ≥18 years, has given birth at least 4 weeks previously and is registered at a participating GP practice. We will exclude mothers whose babies have died or have been removed from their care.

A trial invitation letter and participant information sheet (PIS) will be mailed to potentially eligible women by BWCH, which includes a telephone number to call or a reply slip to return if they are interested in participating. Interested women will undergo telephone screening for eligibility. For women who fulfil the initial screening criteria and are still interested in taking part in the trial, a baseline home visit with a researcher will be organised.

Some additional recruitment strategies may also be used if required:

Posters and flyers advertising the study will be displayed in waiting rooms at participating GP practices.Participants may be informed about the trial directly at appointments with the GP or other healthcare professional post-delivery and prior to the 2-month immunisation appointment in participating GP practices.A researcher may be available at the GP practice on specific clinic dates. The PIMMS-WL researcher will provide potential participants with the letter of invitation and PIS directly either to read at the GP practice or for the participant to take home.

If, after having read the letter of invitation and PIS, a woman is interested in participating, they will contact the PIMMS-WL research team for telephone screening (or be screened by the PIMMS-WL researcher at the GP practice) and a baseline home visit will be arranged as described above.

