### Primary outcome

The primary outcome is the feasibility of undertaking a full-scale phase III cluster RCT, and will include assessment of the following:

Whether the trial is appealing to women (via assessment of the recruitment rate to ensure a full phase III trial is feasible);Whether the intervention is acceptable;Whether the intervention has any adverse impact on infant immunisation rates;The number of women who complete the trial and complete the trial questionnaires.

The decision to proceed will be based on prespecified stop-go criteria (see online supplementary table 3).

10.1136/bmjopen-2019-033027.supp4Supplementary data

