### Decision to progress to the phase III trial

For the phase III trial to take place there needs to be evidence from this feasibility trial of meeting prespecified stop-go rules. The trial is too small to include meaningful and sensitive stop-go criteria regarding the impact of the intervention on immunisation rates. However, we will check that the intervention has not adversely affected usual immunisation rates at each GP practice (as described above). The criteria to proceed to the phase III trial will be based on three criteria: recruitment rate, adherence to weekly self-weighing and registration with the online weight loss programme (POWeR) using the traffic light system shown in online supplementary table 3.

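### Recruitment as a share of the target of 80 is a progress milestone, not a sample proportion: its 95% CI has no valid meaning, and alone it does not measure appeal to women

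*Protocol article*

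**What the plan says.** The protocol article defines the recruitment rate in its Statistical analysis section as the "number of participants who took part in the trial divided by the target recruitment (n=80"). The same section closes its outline with: "Recruitment, adherence and immunisation rates will be summarised as proportions with 95% CIs".

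The target comes from Sample size and recruitment: "We will then aim to recruit 80 participants from these GP practices over 8 months". The number of practices is given there too: "We will recruit 10 to 12 GP practices (clusters) across Birmingham, UK". That section states that no formal sample size calculation was done, and it lists further recruitment routes (posters and flyers, clinicians, a researcher in the practice) for use if needed.

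The purpose of the rate is given under Primary outcome, where appeal to women is to be judged "via assessment of the recruitment rate to ensure a full phase III trial is feasible". Decision to progress to the phase III trial names "three criteria: recruitment rate, adherence to weekly self-weighing and registration with the online weight loss programme (POWeR") and refers to a traffic-light table in the online supplement.

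Directly after the definition, the plan adds: "BWCH will also provide data on the number of invitation letters sent", with the age and ethnicity of the women invited. The article defines no rate from these counts.

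**The concern.** A confidence interval for a proportion describes sampling uncertainty when some of n observed units have a characteristic. Here n is the trial team's own target. No set of 80 women exists of whom a fraction joined, so the planned interval answers no question. It would still look precise next to a figure that feeds the stop-go decision.

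The second problem is what the ratio is asked to show. Appeal to women concerns how many of those offered the trial accept it. A ratio to target has no such denominator, so an easy and a very laborious recruitment can return the same percentage. A reader planning phase III could take full recruitment with a narrow interval as evidence of good uptake, which it is not.

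**Working it through.** **Inputs.** Target 80, planned window 8 months, 10 to 12 practices (Sample size and recruitment). Rate = x/80, with a 95% CI for a proportion (Statistical analysis). The article names no CI method. It gives no calculation behind the 80 and no number of letters, so there is no stated figure to reproduce, and the letter counts below are assumptions.

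**1. The interval as planned.** Exact (Clopper-Pearson) limits for x out of n are the 2.5% point of Beta(x, n−x+1) and the 97.5% point of Beta(x+1, n−x). When x = n the lower limit is 0.025^(1/n) and the upper is 1.

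| Recruits x | x/80 | Exact binomial 95% CI |
|---|---|---|
| 40 | 50% | 38.6% to 61.4% |
| 64 | 80% | 69.6% to 88.1% |
| 72 | 90% | 81.2% to 95.6% |
| 80 | 100% | 0.025^(1/80) = 95.5% to 100% |
| 84 | 105% | does not exist |
| 88 | 110% | does not exist |

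The simple normal interval, p ± 1.96·√(p(1−p)/80), fares no better. At p = 1 it has zero width. At p = 1.05 the variance term is 1.05 × (−0.05) = −0.0525, which has no square root.

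**2. The uncertainty if the count is treated as a count.** Over a fixed window, x is closer to a Poisson count. Its exact limits are half the 2.5% point of chi-square on 2x degrees of freedom and half the 97.5% point on 2x+2.

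- x = 64: 49.3 to 81.7 women, or 61.6% to 102.2% of target (binomial: 69.6% to 88.1%).
- x = 80: 63.4 to 99.6 women, or 79.3% to 124.5% of target (binomial: 95.5% to 100%).

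So the binomial interval is too narrow as well as uninterpretable. The Poisson limits ignore clustering by practice, and realistic intervals would be wider still.

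**3. What the same 100% can hide.** Uptake = 80 / letters sent, with exact binomial limits:

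| Letters (assumed) | Uptake | 95% CI | Reported as x/80 |
|---|---|---|---|
| 400 | 20% | 16.2% to 24.3% | 100% |
| 800 | 10% | 8.0% to 12.3% | 100% |
| 1,600 | 5% | 4.0% to 6.2% | 100% |
| 3,200 | 2.5% | 2.0% to 3.1% | 100% |

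These limits also ignore clustering, and the table treats all 80 women as recruited by letter.

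**4. The accrual rate implied by the plan.** 80/8 = 10 women per month. With 10 practices, 80/(8 × 10) = 1.00 per practice-month (Poisson 95% CI 0.79 to 1.24). With 12 practices, 80/(8 × 12) = 0.83 (0.66 to 1.04).

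**The case against.** The best defence is that percent of target is a familiar feasibility milestone, and that stands. The count can be recovered from it, and with the 8 months and 10 to 12 practices it yields the accrual rates in step 4. A reader might infer that the ratio cannot inform phase III recruitment at all. The documents do not support that.

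A reader might also infer that the criterion has no time limit and could be met simply by recruiting for longer, because the study dates under Trial setting span about 26 months. That does not follow. Those dates cover the whole study, including the 3-month follow-up and later interviews. Sample size and recruitment ties the target to 8 months, and nothing in the article provides for an extension. The formula itself carries no time term, but the thresholds are in a supplementary table that is not shown and may contain one. For the same reason one cannot assert that letters sent play no part in the criterion. The article only defines no rate from them.

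The analysis is also descriptive, without hypothesis tests, and the article does not say that the CI drives the decision. The Statistical analysis section calls itself a brief outline and defers to a separate plan, so the mere absence of further summaries is no fault.

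Finally, letters are an imperfect denominator. The record check before mailing covers age, time since birth and practice registration, but not BMI, although a BMI of at least 25 kg/m² is required. Uptake per letter therefore mixes ineligibility with refusal. That is a good reason to report more than one rate.

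None of this rescues the interval. The definition and the CI are both stated explicitly, and a later analysis plan that follows them inherits the fault.

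**Conclusion.** The point holds in limited form. The 95% CI planned for x/80 has no valid meaning: at the target it reads 95.5% to 100%, against 79.3% to 124.5% of target for a Poisson count, and above 80 recruits it cannot be computed. Taken alone, x/80 does not measure what Primary outcome asks of it, since one and the same 100% is compatible with uptake of 2.5% or 20% over the assumed range of letters.

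The conclusion about the CI rests on the wording of the article and on no assumption. The size of the uptake contrast rests on the assumed letter counts. The Poisson comparison assumes a fixed 8-month window and independent recruits. How far the flaw would affect the stop-go decision cannot be judged without the supplementary thresholds. No estimate of treatment effect is touched.

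**What to change.** Report x/80 at the end of the planned 8-month window as a plain percentage of target, without a CI. Beside it, report three rates with 95% CIs that allow for clustering by practice:

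- women enrolled by the letter route divided by letters sent, with a note that BMI is not checked before mailing, so this rate mixes ineligibility with refusal;
- women enrolled divided by women found eligible at screening;
- women enrolled per practice-month, set against the planned 0.83 to 1.0.

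Record the recruitment route for each woman so that those who came by poster or in-practice contact, who have no letter denominator, are counted separately. Ask at screening whether a letter was also received, because the routes can overlap.

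The cost is a change of wording, one extra screening-log field with that question, and a little more descriptive analysis. The number of letters sent is already to be supplied. The route should be captured at screening, since it is hard to reconstruct afterwards.

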#### Study participants

Women will be eligible if they are aged ≥18 years, are at least 4 weeks postnatal, have a body mass index (BMI) ≥25 kg/m^2^ at the time of recruitment, are able to provide written informed consent and do not meet any of the exclusion criteria (online supplementary table 2). Given that the intervention is embedded in immunisation appointments to be eligible, women need to have not yet attended their child’s first immunisation appointment and to be planning to have their child immunised.

10.1136/bmjopen-2019-033027.supp2Supplementary data

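### The stated immunisation check compares women selected for planning to immunise with each practice's normal rate, and no between-arm difference is stated, so a real fall could be masked

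*Protocol article*

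**What the plan says.** The Primary outcome section lists four things that together decide feasibility. One of them is "Whether the intervention has any adverse impact on infant immunisation rates". The Statistical analysis section sets the measure as "the proportion of babies who attended all three immunisation appointments" and says that it "will be reported for each practice (both groups) and the rate compared with the normal immunisation rate for the practice". The section on the decision to progress repeats the same reference point: "we will check that the intervention has not adversely affected usual immunisation rates at each GP practice".

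Three other statements bear on this:

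- Under Study participants, a woman is eligible only if she is known "to be planning to have their child immunised".
- Under Randomisation, practices are allocated 1:1 to the intervention or to usual care.
- Under Attendance at immunisation appointments, "all practices will be asked to provide data on all immunisation appointments attended by both groups". Attendance is therefore available in the randomised usual-care arm, under the same eligibility rule and the same count.

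No contrast between the arms is described for this outcome. The section on the decision to progress concedes that the trial is too small for a stop-go rule on immunisation. It does not mention that trial women are selected relative to the practice population.

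**The concern.** The plan compares a selected group with a reference that, as far as the text shows, is not selected in the same way. Women who have said that they will immunise can be expected to attend more often than the practice as a whole, even with no intervention. The comparison with the norm therefore mixes two things: any effect of being weighed at the appointment, and the head start from eligibility. The two work in opposite directions, and the error runs towards reassurance.

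The check carries weight. It is a primary-outcome component. Monitoring immunisation uptake at the practices is an explicit purpose of the steering committee, there is no data monitoring committee, and adverse events are not collected. A statement that immunisation was unaffected would be carried into the planning of phase III.

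**Working it through.** The protocol states no immunisation rate, margin or power, so there is no figure to reproduce. The rates and the ICC below are assumptions.

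**Inputs from the protocol.** 80 women, 10 to 12 practices, 1:1 allocation. This gives 80/12 = 6.7 to 80/10 = 8 women per practice, 5 to 6 practices per arm and about 40 women per arm.

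**1. Selection.** Let p0 be the rate in trial women without the intervention, N the practice norm and d the true fall.

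- Intervention practices against the norm: (p0 − d) − N = (p0 − N) − d.
- Intervention minus usual care, in expectation: (p0 − d) − p0 = −d.

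| p0 | N | d | Against norm | Between arms |
|---|---|---|---|---|
| 98% | 90% | 8 | 0 | −8 |
| 98% | 85% | 8 | +5 | −8 |
| 98% | 85% | 13 | 0 | −13 |
| 95% | 85% | 10 | 0 | −10 |
| 90% | 90% | 8 | −8 | −8 |

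The fall is masked up to the size of the gap p0 − N. The last row shows that with no gap there is no masking.

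**2. Precision within a practice (exact Clopper-Pearson 95% intervals).**

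- 8 of 8: 63% to 100%. 7 of 8: 47% to 99.7%.
- One missed baby moves the rate by 1/8 = 12.5 to 1/6.7 = 15 points.
- Against a 90% norm, the interval excludes the norm only at 4 of 8 or fewer, or 3 of 7 or fewer.
- After an 8-point fall from 98% to 90%, the probability of that in a given practice is 0.3% (n = 7) to 0.5% (n = 8). In at least one of 5 to 6 intervention practices it is about 1% to 3%.
- Point estimates can also alarm falsely: one miss among 7 or 8 already puts a practice below 90%.

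**3. Pooling without changing the comparator.** With 40 women at a true 90% after the same fall, the exact interval excludes a 90% norm with probability 1.5%. A larger group does not help while the reference is the norm.

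**4. The between-arm difference, 40 against 40.** The half-width is 1.96 × √(2p(1 − p)/40).

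- p = 0.95: 9.6 points. p = 0.90: 13.1 points.
- With an assumed ICC of 0.05 and 8 women per practice, multiply by √(1 + 7 × 0.05) = 1.162: 11.1 and 15.3 points.
- With 10 practices, replacing 1.96 by t on 8 degrees of freedom (2.31) takes 15.3 to 15.3 × 2.31/1.96 = 18 points.
- For 98% against 90%: 1.96 × √(0.98 × 0.02/40 + 0.90 × 0.10/40) = 10.3 points before clustering. Two-sided power would be about 32%, or 26% to 31% with ICC 0.05 to 0.01.

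These are normal approximations with only about 2 to 4 missed series expected per arm (40 × 0.05 to 40 × 0.10), so they give the order of magnitude only.

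**The case against.** The strongest reply is that the usual-care arm is not left out. Its practices receive the same comparison with their own norms. If selection lifts trial women above the norm, the lift should appear there too, and a reader who sets intervention practices at the norm beside usual-care practices well above it would see the pattern. This stands. A reader might infer that usual-care attendance goes unused, or that a fall is bound to be hidden. The protocol supports neither: the rates are reported for both groups, and a fall larger than the gap would show in expectation. What is missing is a stated contrast between the arms with its uncertainty.

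Other replies also have force:

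- The article calls its analysis section a brief outline and defers to an analysis plan that is not shown. That plan may contain an arm-level summary. Even so, the article names a comparator twice, and both times it is the practice's own rate.
- The small size is conceded and no hypothesis tests are planned. The concession covers size, not selection, and the check is kept in the next sentence.
- The normal rate is not defined, so its coverage of families who never meant to immunise is a reasonable inference, not a stated fact.
- The usual-care comparison is free of this selection bias but not of chance imbalance. With 5 to 6 practices per arm, balanced on list size and deprivation but not on uptake, practices may differ beforehand. The norm does reflect each practice's own level, which is a reason to keep it as context.

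A reader might also infer that practices would misattribute absences, since "Any missed appointments will be investigated and a reason allocated by the GP surgery". Nothing in the protocol shows that they would. Women's own reports of attendance are collected at follow-up, and a sample of intervention women is interviewed.

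**Conclusion.** The concern holds as a flaw in the choice of comparator. As written, the only stated comparison leans towards finding no harm, by an amount equal to the gap between trial women and the practice norm. That amount is unknown. It is 8 or 13 points under the assumed 98% against 90% or 85%, and nil if there is no gap, although the eligibility rule makes a nil gap unlikely. Separately, the practice-level comparison is too small to inform.

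A reader might conclude that the decision to proceed rests on this check. It does not: the three progression criteria are recruitment, weekly self-weighing and registration with the online programme. For that reason, and because both arms' rates will be visible, this is a should-fix and not a bar to the trial.

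**What to change.** - Make the main immunisation summary the intervention-minus-usual-care difference in the proportion attending all three appointments, pooled over practices. Give it descriptively, with a 95% interval that allows for clustering and for the small number of practices. This fits the protocol's emphasis on interval estimation without testing.
- Choose an interval method that still behaves when attendance is close to complete.
- Report the largest fall that the interval does not exclude, in place of a conclusion that rates were not harmed.
- Keep each practice's normal rate as context, define it, and note that trial women were selected for planning to immunise.
- Bring the sections on statistical analysis and on the decision to progress into line with this.

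The data are already to be collected, so the cost is wording. The price in reporting is an openly wide interval, roughly 10 to 15 points or more each side, with chance imbalance between 5 to 6 practices per arm still present. The change removes the selection bias; it does not make the trial able to rule out harm.
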